## Abstract

**Background:**

Atopic dermatitis (AD) has increased rapidly with rapid urbanization; however, the treatment options for AD are lacking because the commonly used therapies can only alleviate symptoms. *Limosilactobacillus reuteri (L. reuteri),* FN041 is a specific strain isolated from human breast milk, and its protective potential against AD has been confirmed. This study aims to assess the efficacy of maternal consumption of *L. reuteri* FN041 during late pregnancy and lactation in preventing infantile AD.

**Methods:**

First, a randomized, double-blind, placebo-controlled intervention study will be conducted on 340 pregnant females with babies at high risk for AD. These subjects will be randomly divided into four groups of different doses of *L. reuteri* FN041 (1 × 10^9^, 5 × 10^9^, and 1 × 10^10^ CFU/d) along with a placebo. The safety and efficacy of maternal use of *L. reuteri* FN041 for preventing infantile AD will be analyzed, and the most efficient dosage of *L. reuteri* FN041 will be determined. Subsequently, a multicenter cohort study of 500 pregnant females with babies at high risk for AD will be conducted to promote the maternal application of *L. reuteri* FN041. These subjects will be administered *L. reuteri* FN041 at the optimal dose determined during the first stage of late pregnancy and lactation, and their babies will be analyzed for AD development. Recruitment was initiated in October 2022.

**Discussion:**

The primary outcome is the cumulative incidence of AD at 24 months after maternal consumption of *L. reuteri* FN041 during late pregnancy and lactation, whereas the secondary outcome is the efficiency of *L. reuteri* FN041 transfer from the mother’s gut to breast milk and then the infant’s gut after oral supplementation. This study will demonstrate the efficacy of edible probiotics isolated from breast milk in preventing or treating AD in infants. Accordingly, we provide population-based advice for administering specific probiotics for the primary prevention of AD in pregnant females. Understanding the underlying mechanisms of probiotic strains derived from breast milk can promote their application in preventing infant diseases associated with intestinal microbiota imbalance and immune disorders.

**Clinical trial registration:**

https://www.chictr.org.cn/, identifier [ChiCTR2300075611].

## Introduction

### Background and rationale

Atopic dermatitis (AD) is an immune-associated inflammatory skin disease characterized by recurrent severe itching and dry skin (Langan et al., 2020). Severe itching affects sleep, growth, and development of young children (Nicholas et al., 2022; Wollenberg et al., 2023). Without effective intervention, infants with AD are susceptible to developing asthma, allergic rhinitis, and conjunctivitis (Elezbawy et al., 2023). The prevalence of AD among urban infants in China is rapidly increasing and similar conditions have been observed in other developing countries (Elezbawy et al., 2023). AD usually occurs early in life. In China in 2019, the total prevalence of AD in infants aged 1–12 months was 30.48%; among which, the incidence in infants aged 3 months was approximately 40.81% (Guo et al., 2019). Currently, clinical therapy commonly involves the use of glucocorticoids and immunosuppressive drugs; however, these drugs alleviate the clinical symptoms of AD only to a certain extent and may cause side effects (Wollenberg et al., 2023). Further, treatment with drugs is challenging in terms of limitations in drug selection for infants and young children (Wollenberg et al., 2023). Therefore, it is necessary to find suitable prevention and therapeutic strategies for infants and young children with AD.

Infant gut microbiota colonization and abnormal immune response are involved in the development of AD (Mahmud et al., 2022). In children with AD, the diversity of the gut microbiota and relative abundance of *Lactobacilli* and *Bifidobacteria* are substantially decreased, whereas the abundance of pathogenic bacteria such as *Escherichia coli*, *Clostridium difficile*, and *Staphylococcus aureus* is notably increased, compared to healthy individuals (Kim and Kim, 2019). Alterations in the gut bacterial community are correlated with disease severity (Kim and Kim, 2019). Previous data have revealed that exclusive breastfeeding in the first 3 months of life is associated with a lower incidence of AD in infants with a family history of allergic diseases (Gdalevich et al., 2001). This protective effect may be related to the microorganisms supplied by breast milk, which ensures a continuous supply of bacteria throughout the lactation period for infants (Lyons et al., 2020).

Interestingly, a recent meta-analysis summarized 21 relevant randomized controlled trials conducted in different countries and confirmed that supplementing mothers with composite probiotics before and after delivery can prevent infantile AD, whereas supplementing infants with probiotics may not effectively prevent the onset of AD (Amalia et al., 2020). Among these studies, five observed that probiotic mixture interventions during pregnancy and lactation reduced the incidence of AD in infants by approximately 28% (Amalia et al., 2020). However, in studies using a single probiotic strain, *lactobacillus rhamnosus* HN001 (HN001) or *lactobacillus rhamnosus* GG (LGG), for maternal supplementation did not reduce the incidence rate of AD in infants (Ou et al., 2012; Wickens et al., 2018). However, supplementation of both mothers and infants with HN001 during pregnancy and lactation can significantly reduce the incidence of AD by 2 years (Wickens et al., 2008). The main reason behind the poor preventive effects of probiotics against AD when administered to mothers during pregnancy and lactation, rather than to infants, may be explained by the fact that probiotics such as LGG cannot be effectively transmitted through breast milk to the infant’s intestines (Simpson et al., 2018). The key to preventing AD in infants via maternal consumption of probiotics is to use strains that can be transmitted from the mother’s gut to breast milk.

The infant gut microbiota changes rapidly in early life and gradually shifts to the adult composition during the first year after birth (Pickard et al., 2017). Breastfeeding has been suggested to be a key factor in establishing the infant gut microbiome (Baldassarre et al., 2018). According to entero-mammary pathway hypothesis, some bacteria in the mother’s gut can be transported to the breast through the lymphatic system and enter the infant’s gut via breast milk (Rodriguez, 2014). Our previous work demonstrated that secretory immunoglobulin A (sIgA)-coated bacteria are the key bacteria for vertical transmission from mother to child (Ding M. et al., 2022; Qi et al., 2022). In the agricultural and pastoral areas of the Gannan Tibetan Autonomous Prefecture of China, the relative abundance of *Limosilactobacillus reuteri* in human milk is far higher than that in other urbanized areas, which may contribute to the low incidence of allergic diseases (Chen, 2013; Ding et al., 2019). We previously used targeted sIgA immunomagnetic bead enrichment and separation technology to isolate a strain of sIgA-coated *L. reuteri* (isolation number FN041, patent strain storage number GDMCC60546) from the breast milk of Gannan females. This strain is included in the list of bacterium strains that can be used for food released by the National Health Commission and is a probiotic that can be used in ordinary food.

We also observed that maternal supplementation with *L. reuteri* FN041 during late gestation and lactation, along with offspring supplementation with *L. reuteri* FN041 after weaning, could effectively protect against AD (Zhao et al., 2022). In mice, the protective effect of maternal intervention with the sIgA-coated *L. reuteri* strain, which can be transmitted to milk, may modulate the intestinal microbiota community and the immune response of the offspring (Zhao et al., 2022; Qi et al., 2023). Moreover, further research has proven that the protective effect imparted by maternal supplementation with *L. reuteri* FN041 was much stronger than that imparted by the *L. reuteri* FN041 supplementation only in infant mice to prevent AD after weaning (Zhou et al., 2022). Therefore, assuming that maternal consumption of *L. reuteri* FN041 during pregnancy and lactation may be effective in preventing AD in offspring, we conducted a randomized controlled trial to provide data on this primary prevention strategy for AD.

### Objectives

This study aims to assess the incidence of infantile AD after maternal consumption of *L. reuteri* FN041 during late pregnancy and lactation. The optimum dosage will be determined by analyzing the efficacy of maternal supplementation with different doses of *L. reuteri* FN041 in preventing AD in offspring. Additionally, the secondary objective is to identify the transfer efficiency of *L. reuteri* FN041 from the mother’s gut to breast milk and then to infant’s gut after oral supplementation.

### Trial design

The study is divided into two stages. In the first stage, a multicenter, randomized, double-blind, placebo-controlled intervention study will be conducted in 340 pregnant females with babies at high risk for AD recruited from the Wuxi Maternity and Child Health Care Hospital affiliated with Jiangnan University and the Affiliated Hospital of Qingdao University. These subjects will be randomly divided into four groups (*n* = 85 for each group): (1) placebo group administered with the carrier solid beverage daily, (2) group administered with *L. reuteri* FN041 solid beverage at a dose of 1 × 10^9^ CFU/d, (3) group administered with *L. reuteri* FN041 solid beverage at a dose of 5 × 10^9^ CFU/d, and (4) group administered with *L. reuteri* FN041 solid beverage at a dose of 1 × 10^10^ CFU/d. Their offspring will be examined for AD development during the 2 years after birth so that the efficacy of maternal use of *L. reuteri* FN041 in the prevention of AD can be analyzed by calculating the cumulative incidence of AD in infants. Adverse reactions will be also recorded. Studies have reported that the most efficient dosage of *L. reuteri* FN041 can be determined within 6 months after birth, as infantile AD often develops in early life and peaks in the third month of life (Guo et al., 2019).

In the second stage of *L. reuteri* FN041 promotion and application, a multicenter cohort study in an expanded research population will be conducted. A total of 500 pregnant females with babies at a high risk for AD will be recruited from four tertiary hospitals: Wuxi Maternity and Child Health Care Hospital affiliated with Jiangnan University, Affiliated Hospital of Qingdao University, Suzhou Municipal Hospital, and Changzhou Maternal and Child Health Hospital. These subjects will be administered with *L. reuteri* FN041 at the optimal dosage determined in the first stage during late pregnancy and lactation; subsequently, their babies will be followed up for AD development for 2 years after birth.

## Methods

### Eligibility criteria

According to the World Allergy Organization guidelines, a child may be considered at high risk for allergy if a biological parent or sibling has a history of allergic rhinitis, asthma, eczema, or food allergy (Fiocchi et al., 2015). The recruited pregnant females with babies at high risk for AD must meet the following inclusion criteria: healthy pregnant female (14–16 weeks of gestation), the mother or father of the fetus, or previous child of the couple diagnosed with any of the allergic diseases, including asthma, eczema, food allergy, or allergic rhinitis. This information will be confirmed by specific recruiters prior to recruitment. The risk of developing AD in infants without a family history of allergies is approximately 27%, whereas that in infants with one or two parents with an atopic history increases to 37.9 and 50.0%, respectively (Böhme et al., 2003). The population we aim to recruit meets the recommended probiotic target audience according to the guidelines of the World Allergy Organization (Fiocchi et al., 2015). The exclusion criteria are as follows: pregnant female under 16 years of age, multiple pregnancies, known fetal abnormalities, oral administration of immunosuppressive drugs or antibiotics, heart valve disease or immunodeficiency, undergoing dental surgery under antibiotic prevention, history of transplantation or HIV, long-term continuous use or ongoing use or intent to use probiotics before admission, external fertilization pregnancy, previous participation in research, deemed unsuitable for inclusion in the study owing to other medical reasons, and gestational diabetes.

### Sample size calculation

The cumulative incidence of AD in high-risk infants at 1 and 2 years of age is reported to be approximately 40.1 and 41%, respectively, based on previous studies conducted in other countries (Rautava et al., 2012; Chaoimh et al., 2023). According to a previous study carried out in 2022 in our hospital, the overall point prevalence of AD in infants aged 0–24 months was 50.5% in Wuxi (Ding Y. et al., 2022). The expected cumulative incidence of AD after *L. reuteri* administration is approximately 20%, with a relative 20% reduction in AD incidence of 40% through intervention. Assuming that the first type of error would be 2.5% and the efficacy would be 80%, we calculated the sample using online tools.^1^ The sample size in each group would be 74. Considering a 10% dropout rate, each group should recruit 85 research subjects in the first stage. In the second stage of the trial, the sample size is expected to be approximately 500, which is considered sufficient to further verify the efficacy of maternal use of *L. reuteri* FN041 in the prevention of infantile AD.

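### The 40% placebo rate is not reconciled with the 50.5% cited from Wuxi, and the stated 80% power is not delivered for a 20-point reduction at placebo rates of 40–50%

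*Protocol article*

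**What the plan says.** Protocol article, Sample size calculation: the 1- and 2-year cumulative incidence in high-risk infants is given as "approximately 40.1 and 41%, respectively, based on previous studies conducted in other countries". The next sentence, citing a study in the investigators' own hospital, states that "the overall point prevalence of AD in infants aged 0–24 months was 50.5% in Wuxi". The calculation then uses about 20% on FN041, "with a relative 20% reduction in AD incidence of 40% through intervention". With a 2.5% type I error and 80% (called efficacy, read here as power), it arrives at 74 per group, raised to 85 for 10% dropout.

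Other rates appear elsewhere in the article:
- **Background and rationale:** 30.48% prevalence in Chinese infants aged 1–12 months, "among which, the incidence in infants aged 3 months was approximately 40.81" per cent.
- **Eligibility criteria:** about 27% without a family history, "whereas that in infants with one or two parents with an atopic history increases to 37.9 and 50.0%, respectively".

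Trial design names Wuxi as one of two stage 1 hospitals. The primary outcome is the cumulative incidence of AD within 2 years of delivery. Statistical methods sets a two-sided 5% significance level.

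**The concern.** In one population under one case definition, the point prevalence at any age up to 24 months cannot exceed the cumulative incidence to 24 months. If the 50.5% described the infants of this trial, it would be a floor for the placebo rate. The Wuxi figure is also not described as restricted to high-risk families, whereas the trial enrols only those. So either the Wuxi figure does not carry over, because of its sample or case definition, or 40% is low for that site. The section prints both figures and says neither.

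What is at stake is the meaning of the 80%. The effect is called a relative 20% reduction, although 40% to 20% is 20 points absolute and 50% relative. A reader who moves the placebo rate towards 50% cannot tell whether to carry over the 20 points, the halving or the 20% treated rate, and these lead to very different power.

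**Working it through.** **Inputs.** Placebo 40%, FN041 20%, 74 evaluable per group, 80% power (Sample size calculation). The sidedness of the 2.5% is not stated. I read it as one tail, equivalent to the two-sided 5% in Statistical methods. This is the reading more favourable to the plan.

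**Formulas.** Two-proportion z-test, equal groups, pooled variance under the null. With D = p1 − p2, m = (p1 + p2)/2, A = 1.960 × √[2m(1 − m)] and B = √[p1(1 − p1) + p2(1 − p2)]:
- power = Φ[(D√n − A)/B]
- n for 80% power = (A + 0.8416 × B)²/D²

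**The plan's own figure first.** 40% vs 20%: m = 0.30, A = 1.960 × √0.42 = 1.270, B = √0.40 = 0.632.
- n = (1.270 + 0.532)²/0.04 = 81.2, so 82 per group. The unpooled version gives 79, the arcsine version 81 and a continuity correction 91. None gives 74.
- A two-sided 2.5% test would need 99.
- The nearest matches depart from the stated inputs: 41% vs 20% gives 75 (74 by arcsine), and 40% vs 20% at one-sided 5% with continuity correction gives 74.
- Power at 74: (0.2 × 8.602 − 1.270)/0.632 = 0.712, and Φ = 76%.

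**Placebo rate varied, 74 per group, two-sided 5%.**

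| Placebo vs FN041 | What is carried over | Power | n per group for 80% |
|---|---|---|---|
| 40% vs 20% | planned pair | 76% | 82 |
| 45% vs 25% | 20 points | 73% | 89 |
| 50.5% vs 30.5% | 20 points | 70% | 94 |
| 50.5% vs 25.25% | halving | 89% | 57 |
| 50.5% vs 20% | treated rate (60% relative reduction) | 98% | 38 |

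For 50.5% vs 30.5%: m = 0.405, A = 1.361, B = √(0.2500 + 0.2120) = 0.680; (1.720 − 1.361)/0.680 = 0.529, and Φ = 70%.

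**Sensitivity to the number analysed.** 85 × 0.9 = 76.5. At 76 per group the three 20-point rows become 77%, 74% and 71%. If all 85 were evaluable, 0.2 × √85 = 1.844 and the rows become Φ(0.907) = 82%, Φ(0.791) = 79% and Φ(0.711) = 76%.

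**The case against.** A reader might infer that 40% is too low, or that it does not describe the high-risk infants being enrolled. The documents do not support that:
- The 40.1% and 41% are the only cited rates that are both in high-risk infants and cumulative to 1 and 2 years, so they match the endpoint. Foreign origin alone does not make them wrong.
- 40% lies inside the 37.9–50.0% quoted for one or two atopic parents.
- The Chinese figures do not all lie above 40%. One is 30.48%, and 40.81% is practically 40% (it changes n by at most 6 per group). That leaves 50.5% as the only figure clearly above it.
- The sample and case definition behind the 50.5% are not described, and no rate is given for Qingdao, the other stage 1 site.

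A reader might also infer that a higher placebo rate makes the trial too small. That does not follow either. Power rises to 89% if the halving carries over and to 98% if the treated rate stays at 20%; for a relative effect, 40% is the cautious choice. Most of the shortfall is already there at the planned pair: power is 76% at 40% vs 20%, and moving to 50.5% vs 30.5% takes off about 6 points more.

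All of this stands, and it limits the point to two things: the two rates are left unreconciled, and the 80% is not what the design delivers for the difference it plans on.

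**Conclusion.** The point holds in this limited form. The choice of 40% is defensible but not defended against the 50.5% printed beside it. For a 20-point reduction, power at 74 evaluable per group is about 76% at a 40% placebo rate, falling to about 70% at 50.5%. It does not reach 80% anywhere in that range.

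This rests on a pooled two-proportion z-test at two-sided 5%, on one dose compared with placebo, and on 74 evaluable per group. Allowing for the planned 10% loss from 85 adds about one percentage point. Only with no loss at all does power pass 80%, and then at 40% vs 20% but not at 45% vs 25%. If the effect is relative and the true placebo rate is near 50%, power is about 89% and there is no shortfall. The documents do not settle which holds.

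**What to change.** In Sample size calculation:
1. Keep 40% as the base case and add a sentence saying why the Wuxi 50.5% is set aside. The match of the foreign rates to the risk group, measure and time horizon is available as a reason. Any difference in sample or case definition should be stated if the sponsor can confirm it.
2. Name the effect once, as a 20-point absolute (50% relative) reduction from 40% to 20%.
3. Replace 80% with the power of the fixed sample over placebo rates of 40–50%: about 76% (40% vs 20%), 73% (45% vs 25%) and 70% (50.5% vs 30.5%) at 74 evaluable per group, two-sided 5%. Note that power would be about 89% at 50.5% if the halving carries over.

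Two further steps may suggest themselves, and I do not recommend either. Making 50% the base case would replace a matched rate with a point prevalence from an undescribed sample. A pooled blinded rate at 6 months cannot identify the placebo rate with one placebo and three active arms: a pooled 30% fits (40 + 3 × 26.7)/4 and equally (60 + 3 × 20)/4.

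The cost is one reworded paragraph and a less favourable power statement. Enrolment stays at 85 per group.

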### Interventions

#### Intervention strategy

The *L. reuteri* strain used in this study is a probiotic supplement derived from breast milk and formulated in the form of a solid beverage with highly acceptable properties. The solid beverage contained fructooligosaccharides, erythritol, stachyose, resistant dextrin, strawberry juice powder, and vitamin C. The products of the solid beverages with and without *L. reuteri* have the same taste and are packed at 1.5 g per package. *Limosilactobacillus reuteri* has been reported to colonize the intestines of almost all vertebrates and mammals, has good biocompatibility, and is widely used for food production. We previously used targeted sIgA immunomagnetic bead enrichment and separation technology (patent number ZL201610975479. X) to isolate a strain of sIgA-coated *L. reuteri* FN041 (patent strain storage number: GDMCC60546) from Gannan breast milk. This species is included in the list of bacterium strains that can be used for food released by the National Health Commission and is a probiotic that can be used in ordinary food. Genome sequencing analysis revealed that *L. reuteri* FN041 has no horizontally transmissible antibiotic resistance or pathogenic genes.

The selected doses (1 × 10^9^, 5 × 10^9^, and 1 × 10^10^ CFU/d) of *L. reuteri* FN041 in the first stage are in the reported safe range and the optimal dosage will be determined and subsequently applied in the second stage. The World Allergy Organization recommends probiotic administration to pregnant females at high risk of bearing a child with allergy during pregnancy and, in case of breastfeeding, lactation (Fiocchi et al., 2015). Therefore, oral intervention with the respective solid drinks for the recruited subjects in the two stages will start from the gestational age of 32–36 weeks until delivery. The mothers will continue to consume the corresponding solid drinks daily for 6 months, from 1 to 3 days after delivery, during the lactation period. All the solid drinks are suggested to be taken orally at bedtime once daily.

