#### Allocation and blinding

The participants recruited in this study will be grouped randomly in the first stage of project implementation so that they are consistent with each group according to their age, economic situation, educational level, and other influencing factors.

In the first stage, both the on-site and laboratory analyses will be conducted using a double-blind method. The samples of *L. reuteri* and placebo used in the experiment will be processed and produced by a third-party company. The project organizer, researchers, and participants will not be informed about the intervention methods they receive. The biological samples analyzed by laboratory technicians (including blood, breast milk, and feces) will be blinded to their specific sources and grouping situations until the end of all experiments.

In the second stage, a multicenter cohort study will be conducted, in which the recruited subjects will not be blinded because this stage has been designed to explore the efficacy of maternal intervention with *L. reuteri* in preventing infantile AD.

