### Outcomes

#### Primary outcomes

In both stages of the trial, the cumulative incidence of AD within 2 years of delivery will be analyzed as the primary outcome. The diagnosis of AD is based on the Williams standard, as previously described, which is widely applicable to outpatient and general population epidemiological investigations in research (Williams et al., 1994). Skin itching is the primary criterion. The secondary criteria are as follows: (1) history of skin involvement on the flexor side, including the cubital fossa, cochineal fossa, anterior malleolus, and neck; (2) history of asthma, allergic rhinitis, or AD in first-degree relatives of children under 4 years of age; (3) history of dry skin throughout the body; (4) eczema on the flexed side (on the cheek or forehead and limbs on the extended side in children under 4 years of age); and (5) onset before the age of 2 years. Infants who meet the main criteria, along with three or more secondary criteria, will be diagnosed with AD. Once diagnosed with AD, disease severity will be assessed using the SCORAD index. Accordingly, infants will be divided into mild (SCORAD: 0–24 points), moderate (SCORAD: 25–50 points), and severe (SCORAD: >50 points) groups (Oranje et al., 2007).

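### Stage 2 treats all 500 women unblinded with no stated comparator, so it can estimate AD incidence but cannot by itself verify efficacy

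*Protocol article*

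**What the plan says.** In the protocol article, the Trial design section says of stage 2 that "a multicenter cohort study in an expanded research population will be conducted". It draws 500 women from four hospitals, two of which take no part in stage 1. All of them receive FN041 "at the optimal dosage determined in the first stage during late pregnancy and lactation".

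The Allocation and blinding section says that "the recruited subjects will not be blinded because this stage has been designed to explore the efficacy of maternal intervention with" the strain. The Primary outcomes section covers both stages: "In both stages of the trial, the cumulative incidence of AD within 2 years of delivery will be analyzed as the primary outcome".

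On size, the Sample size calculation section says only that "the sample size is expected to be approximately 500", "which is considered sufficient to further verify the efficacy of maternal use of" FN041. It attaches no significance level, power, reference rate or precision target to that number.

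Two other places describe stage 2 more modestly. The Abstract speaks of promoting use of the product. The Discussion speaks of finding out how often AD occurs once mothers have taken it.

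**The concern.** Efficacy is a contrast between what happened with the product and what would have happened without it. Stage 2, as described, has one treated group and nothing to set it against. A larger sample narrows the interval around that group's incidence, but it does not supply the missing side of the comparison. The sufficiency claim therefore gives the design a property it lacks. Offering the study of efficacy as the reason for leaving women unblinded adds to the problem, because knowledge of treatment weakens an efficacy inference.

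The article intends its results to support advice on probiotic use in pregnancy. A low incidence among 500 treated women could be presented as confirming stage 1 when it would only be compatible with it.

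**Working it through.** **Reproducing the 500.** No hypothesis, reference rate, error rate or precision target is given for stage 2, so the figure cannot be re-derived.

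**What 500 women in one arm deliver.** Inputs: expected incidence 20% (Sample size calculation); n = 500; and n = 500 × 0.90 = 450 if the 10% dropout planned for stage 1 also applies to stage 2, which is my assumption. The 95% half-width is 1.96 × √(p(1 − p)/n).

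- n = 500: 1.96 × √(0.20 × 0.80/500) = 0.0351, or 3.5 points.
- n = 450: 1.96 × √(0.20 × 0.80/450) = 0.0370, or 3.7 points.

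This is good precision for an incidence.

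**What an efficacy reading would need.** The article gives these rates that resemble the endpoint and population: 37.9% with one or two atopic parents listed separately (this is the one-parent figure, Eligibility criteria), and 40.1% at 1 year and 41% at 2 years in high-risk infants abroad (Sample size calculation). None is named as the stage-2 reference. Their spread is 41 − 37.9 = 3.1 points, slightly less than the half-width.

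Even within this narrow range the error rate is not fixed until a reference is named. Suppose the product does nothing and the true background is 40%, the article's planning rate. An exact one-sided 2.5% binomial test with n = 500 would then declare benefit as follows:

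| Reference rate | Benefit declared if cases ≤ | Probability with no true effect |
|---|---|---|
| 37.9% | 167 | 0.1% |
| 40% | 178 | 2.4% |
| 41% | 183 | 6.5% |

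**What a reference rate would not remove.** Four features could move the stage-2 incidence without any effect of the strain:

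- *Family-history mix.* The article puts risk at 37.9% with one atopic parent and 50.0% with two, a gap of 12.1 points. If the share of two-parent families differs by 10 percentage points between the cohort and the reference, the expected incidence moves by 0.10 × 12.1 = 1.2 points. The 10 points is only an illustration, as the article gives no expected mix.
- *Hospitals.* Two of the four sites are new in stage 2.
- *Carrier.* "The solid beverage contained fructooligosaccharides, erythritol, stachyose, resistant dextrin, strawberry juice powder, and vitamin C". Stage 1 controls for these with a carrier placebo. Stage 2 has no such group.
- *Ascertainment.* The Participant timeline section relies partly on parents bringing a child they suspect of having AD, and stage-2 parents know the exposure.

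**The passages side by side.** The descriptive aim in the Discussion is achievable with this design. The aims in the Sample size calculation and Allocation and blinding sections are not.

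**The case against.** Five points can be made for the plan.

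- *This is a condensed article, and an unseen protocol or SAP may name a comparator.* That could be so for a historical or stage-1 reference. It cannot supply a concurrent control among these 500, because the article commits all of them to the product.
- *The stage-1 placebo group could serve.* The article does not say so. That group would be 85 blinded women from two of the four hospitals, recruited from July to December 2023, whereas stage 2 recruits from July to December 2024. Such a comparison would be non-concurrent.
- *If 20% is observed, the result is hardly ambiguous.* The interval's upper end would be 20 + 3.5 = 23.5%, or 23.7% with 450 infants. That is below every comparable rate, and below the 27% quoted for infants without a family history. This stands: under the planning assumption, sampling error is not the difficulty. The difficulty is attributing the gap to the strain.
- *Diagnosis does not rest on parents alone.* The Participant timeline section schedules hospital visits at 1, 3, 6, 8 and 12 months and joint diagnosis by two dermatologists. This also stands, so parent reporting is one route among several. After 12 months, though, that section lists only a telephone contact at 24 months and parent-initiated visits.
- *Randomised stage 1 is the efficacy test, and the Discussion already describes stage 2 as estimating incidence.* Agreed. That is why the fix is a matter of wording.

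**Conclusion.** The sufficiency claim is wrong as written. Stage 2 can estimate the 24-month cumulative incidence of AD under open-label use to within about 3.5 to 3.7 points at 20%. It cannot by itself verify efficacy. This rests on the article's statement that all 500 women receive the selected dose unblinded, and on its naming no comparator, reference rate or hypothesis for the stage.

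A reader might infer three stronger things that the documents do not support.

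- *That the possible reference rates are scattered far more widely than the cohort's precision, from 37.9% up to 50.5%.* The 50.5% is a point prevalence in local infants overall, and the 50.0% applies only to infants with two atopic parents. The comparable figures span 3.1 points.
- *That choosing the best of three doses biases stage 2.* It can flatter the selected arm's stage-1 estimate. The stage-2 incidence comes from newly recruited women and does not inherit that bias.
- *That stage 2 must be redesigned.* Its descriptive aim in the Discussion is sound for the design described. Only the efficacy wording exceeds it.

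**What to change.** 1. In the Sample size calculation section, replace the sufficiency claim with: *Stage 2 estimates the 24-month cumulative incidence of AD, and safety, under open-label use of the selected product. With 500 infants the 95% confidence interval is about ±3.5 percentage points at an incidence of 20% (±3.7 with 450 evaluable).* This agrees with the aim in the Discussion.
2. In the Allocation and blinding section, remove exploration of efficacy as the reason for not blinding, and simply describe stage 2 as an open-label cohort.
3. State once that efficacy conclusions come from the randomised stage-1 comparison with placebo.

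The cost is a few sentences and a weaker stage-2 claim. Participants, visits and data collection do not change.
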